## Standardised assessment description

All chosen standardised assessments are valid, reliable and responsive to change. Validated German versions will be used as can be seen from the CRF.

The Functional Ambulation Categories (FAC) (Mehrholz et al., 2007; Wade, 1992) will be used in its validated German version (Klotz et al., 2019) to screen patients with respect to their walking ability and to assess walking ability post-intervention. The FAC is a 6-point functional walking test that evaluates ambulation ability, determining how much human support the patient requires when walking, regardless of whether or not they use a personal assistive device. The FAC is a quick visual measurement of walking, is simple to use, easy to interpret, and cost-effective because only stairs and 15m of indoor floor are needed to administer the test

The 10-Metre Walk Test (10MWT) (Bohannon, 1997) is a performance measure used to assess walking speed in meters per second over a short distance. It can be employed to determine functional mobility in various neurological populations. The 10MWT was originally developed to measure walking capacity in patients with stroke (Wade et al., 1987) and was shown to be valid and reliable in a mixed group of neurological patients (Rossier & Wade, 2001). Its psychometric properties have been well investigated in adult patients with incomplete spinal cord injury showing good reliability and excellent responsiveness (van Hedel et al., 2006; van Hedel et al., 2005). In these patients, walking speed could also predict functional walking performance well (van Hedel, 2009). In adult patients with stroke, the 10MWT proved sensitive to change (Salbach et al., 2001). The required equipment includes a stopwatch and a clear pathway with set a distance of 10 metres. The set-up involves marking the 10-metre walkway and adding a mark at 2 and 8 metres. Instructions are as follows: The patient walks without assistance for 10 metres, with the time measured for the intermediate 6 meters to allow for acceleration and deceleration. Assistive devices may be used but must be kept consistent and documented for each test. Timing is started when the toes pass the 2-metre mark and timing is stopped when the toes pass the 8-metre mark. The 10MWT can be tested at either preferred walking speed or maximum walking speed. In this clinical investigation the test will be performed at maximum speed. Two trials will be performed and the average calculated (Watson, 2002).

The Functional Gait Assessment (FGA) (Wrisley et al., 2004) will be used to assess dynamic balance during walking and assess a patient's ability to perform multiple motor tasks while walking. The FGA consists of 10 items. The items address walking on a surface without incline at different speeds, with head turns, with quick turns and stops, climbing stairs and climbing obstacles. The individual items are assessed on a scale of 0-3 points, with 3 points representing the best possible performance of the task. The total number of points is 30. The more points are achieved, the better the dynamic balance of the test subjects. The implementation takes 5-20 minutes (Thieme et al., 2009).

The 6-Minute Walk Test (6MWT) will involve participants covering as much ground as possible in 6 minutes, with or without their assistive devices and without physical assistance, along a 30-metre hallway, with small cones at each end to mark the turnaround points. Warm-up will not be allowed before the test, as recommended by the American Thoracic Society (A. T. S.) guidelines for the 6MWT (2002). Participants will rest on a chair for at least 10 minutes, close to the starting line of the test. A second chair for rest will be positioned close to the end of the hallway, but out of the walking way. Assistive devices can be used, but will be kept consistent and documented from test to test. Participants will be instructed to turn at each end; rests are allowed at any time, and the number and duration of rests during the 6 minutes are measured (Potter et al., 2014). Standard phrases of encouragement by use of an even voice are provided every minute, but no other words of encouragement or body language are used (A. T. S. Committee on Proficiency Standards for Clinical Pulmonary Function Laboratories, 2002). The number of laps from the starting point is counted and recorded visible to the participant, and the number of metres in the final partial lap distance is marked after 6 minutes. The residual walking distance is measured with a calibrated measuring wheel.

The Timed-Up and Go (TUG) will be used to measure functional mobility (Podsiadlo and Richardson, 1991). The TUG can be used as an indicator of the risk of falling during everyday movement tasks. The activities tested are transferring from sitting to standing, walking, turning around in space, going back to the chair and sitting down. For everyday locomotion and reducing the risk of falling, the skills of transferring from sitting to standing and turning in space are of crucial importance (Cheng et al., 1998; Mong et al., 2010). The test begins in the seat, on a chair with a seat height of approx. 46 cm. For the implementation of the TUG, the time that the patient needs to get up from the chair, walk a distance of three meters, turn around, go back three meters to the chair and get back into it, is stopped to move to the starting position. The time required is documented in seconds. Walking aids may be used. All aids used must be documented. The TUG takes less than 5 minutes to complete.

The Four Step Square Test (FSST) (Dite and Temple, 2002) assesses balance and the ability to climb over obstacles forwards, sideways and backwards. The patients stand in a square created by a marked test cross on the floor (see CRF). The patients are asked to step clockwise and then counterclockwise into all four squares. To do this, they have to step forward, to the side and backwards over the marked test cross. There are always two runs, a test run and a run in which the time is stopped. The implementation time is less than 5 minutes.

The Trunk Control Test (TCT) (Franchignoni et al., 1997) will be used in its German version (Fischer, 2014) to assess trunk mobility in severely affected, non-ambulatory stroke patients in the subacute stage. The TCT assesses four movement activities: rolling from a supine position to the weak side (1) and to the strong side (2), sitting up from a lying-down position (3), and sitting balance (4). The scoring is as follows: 0, unable to perform movement

without assistance; 12, able to perform movement but in an abnormal manner; and 25, able to complete movement normally. The TCT score is the sum of the scores obtained on the four tests (range, 0 to 100) (Franchignoni et al., 1997; Hsieh et al., 2002).

The Modified Functional Reach Test (MFRT) will be used to assess the limits of stability with respect to trunk movements in severely affected, non-ambulatory stroke patients in the subacute stage. The MFRT is a modified version of the Functional Reach Test (Duncan et al., 1990) assessing the limits of stability by measuring the maximum distance a patient can reach forward while sitting in a predefined position (Katz-Leurer et al., 2009; Persson et al., 2014). The MFRT is performed using a leveled meterstick attached to the wall at the height of the patient's acromion level of the non-affected arm while sitting on a chair near the wall (Katz-Leurer et al., 2009). The patient is seated with hips, knees and ankles positioned at 90° of flexion, and feet positioned flat on the floor. Initial reach is measured with the patient sitting against the wall with an upper limb flexed to 90°. The initial reach is measured with the patient sitting against the back of the chair with the upper limb flexed to 90 degrees, measure is taken from the distal end of the third metacarpal along the meterstick. Testing consists of three conditions, each containing three trials: Sitting with the unaffected side near the wall and leaning forward (1); sitting with the back to the wall and leaning right (2) and sitting with the back to the wall leaning left. Instructions include leaning as far as possible in each direction without rotation and without touching the wall. The distance is recorded in centimetres covered in each direction. If the patient is unable to raise the affected arm, the distance covered by the acromion during leaning is recorded. The first trial in each direction is a practice trial and is not included in the final result. A 15 second rest break is provided between trials (Katz-Leurer et al., 2009).

A large number of people with neurological disabilities and older people have psychological problems associated with falls. This applies both to patients who have already fallen and to those who have not yet fallen. In order to be able to address these problems, an assessment of the fear of falling and of self-efficacy in relation to falling is required. The Falls Efficacy Scale (Tinetti et al., 1990) was expanded to an international version (FES-I) in 2005 by an expert network for fall prevention (Prevention of Falls Network Europe, ProFaNE) (Yardley et al., 2005; Skelton et al., 2004). The PROM is used to record the fall-associated self-efficacy in patients. With the expansion, more complex, functional activities and social aspects of self-efficacy were added. The FES-I consists of 16 items that evaluate concerns about falls and various activities among the subjects. The questionnaire can be carried out as a self-assessment form or as a structured interview. The answers are classified using a 4-point Likert scale from 1 = "no concerns" to 4 = "very serious concerns". The duration of the questionnaire administration is 5-10 minutes.

The 5-level EQ-5D version (EQ-5D-5L) (Herdman et al., 2011) will be used in its validated German version (Ludwig et al., 2018; Ludwig et al., 2017) to assess health-related quality of life (HRQoL). The EQ-5D-5L was introduced by the EuroQoL Group in 2009 to improve the

instrument's sensitivity and reduce ceiling effects, as has been observed for the EQ-5D-3L. The EQ-5D-5L essentially consists of 2 pages: the EQ-5D descriptive system and the EQ visual analogue scale (EQ VAS). The descriptive system comprises five dimensions: mobility, self-care, usual activities, pain/discomfort and anxiety/depression. Each dimension has 5 levels: no problems, slight problems, moderate problems, severe problems and extreme problems. The patient is asked to indicate his/her health state by ticking the box next to the most appropriate statement in each of the five dimensions. This decision results in a 1-digit number that expresses the level selected for that dimension. The digits for the five dimensions can be combined into a 5-digit number that describes the patient's health state. The EQ VAS records the patient's self-rated health on a 0-100 vertical visual analogue scale, where the endpoints are labelled 'The best health you can imagine' and 'The worst health you can imagine'. The VAS can be used as a quantitative measure of health outcome that reflect the patient's own judgement.

The BDI-II (Beck et al., 1988) will be used to measure the severity of depression and is a secondary endpoint of this clinical investigation. The BDI-II consists of 21 items and is a PROM for recording the severity of the depression. The items are evaluated using a 4-point Likert scale from 0 to 3. This means that the sum of the items can be 0-63 points. The scale is validated from the age of 13 years. The duration of the questionnaire administration is 5-10 minutes.

The Fatigue Severity Scale (FSS) (Krupp et al., 1989) will be used in its validated German version (Valko et al., 2008) to assess fatigue in this clinical investigation. The FSS is one of the most frequently used inventories for measuring fatigue in people with chronic illnesses including those with neurological diseases. The original FSS is a nine-item unidimensional questionnaire. Each item consists of statements that are scored on a seven-point Likert type scale ranging from 1 ('strongly disagree') to 7 ('strongly agree'). The mean score of the items will be used as the FSS score and a cut-off score of 5 to indicate substantial fatigue (Pfeffer, 2008).

Goal Attainment Scaling (GAS) is an example of an individualised evaluative instrument, which is used for measurement of changes in individual patients and groups of patients based on self-selected goals. A 5-point Likert scale was developed by Kiresuk and Sherman (Kiresuk & Sherman, 1968). The following scores apply: - 2, much worse than expected; -1, somewhat worse than expected; 0, expected goal; + 1, somewhat more than expected, and + 2, much more than expected. The GAS proved applicable to patients with acquired brain lesions (Bouwens et al., 2009). In pediatric rehabilitation, the GAS has been shown to be reliable, as reported by a review on the validity, reliability and sensitivity of goal setting (Hurn et al., 2006).

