Patients post stroke are usually treated intensively in the acute and subacute phases to enhance motor performance. This is because the recovery of walking and further sensorimotor and cognitive functions mainly takes place within the first 11 weeks after a stroke. A principle here is: the milder the paralysis, the faster the recovery (Jørgensen et al., 1995). As for patients with more severe disability, *the* principle of neurorehabilitation is 'use it or lose it' [function] (Shors et al., 2012). In patients with amyotrophic lateral sclerosis (ALS), training is more intensive in the first, so called active phase after diagnosis, when the physical condition is better, in order to maintain the walking and other motor functions for as long as possible (Calabrò et al., 2019). In patients with a progressive disease such as MS, Parkinson's, ALS or hereditary ataxias, a main reason for undergoing neurorehabilitation is to preserve their ability to walk (Cheng et al., 2012; Wirz et al., 2001). Neurological deficits, such as walking impairment, poor coordination and balance loss, can be reduced by intensive and repetitive task-oriented training (Nilsson et al., 2001; Van Peppen et al., 2004).

Motor learning is present in patients with mild to severe disability, based on the process of neural plasticity, and can be boosted by a range of neurorehabilitation strategies (Maier et al., 2019). The principles underlying effective neurorehabilitation are well-known yet, and these are applied in inpatient and outpatient neurorehabilitation on a routine basis. A relevant review has identified the most salient principles of motor learning based on the evidence so far. These comprise massed practice, dosage, task-specific practice, goal-oriented practice, variable practice, increasing difficulty, explicit feedback in terms of knowledge of results and implicit feedback in terms of knowledge of performance (Maier et al., 2019).

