### **2.3. Secondary objectives**

Secondary objective 1 of this clinical investigation is to investigate the changes in the fall-rate after a 4-week RAGT as assessed narratively by the number of falls in ambulatory patients.

Secondary objective 2 of this clinical investigation is to investigate the changes in walking ability after a 4-week RAGT as assessed by the Functional Ambulation Categories (FAC).

Secondary objective 3 of this clinical investigation is to investigate the changes in walking speed after a 4-week RAGT as assessed by the 10-Metre Walk Test (10MWT) in ambulatory patients.

Secondary objective 4 of this clinical investigation is to investigate the changes in dynamic balance after a 4-week RAGT during walking as assessed by the Functional Gait Assessment (FGA) in ambulatory patients.

Secondary objective 5 of this clinical investigation is to investigate the changes in walking distance after a 4-week RAGT as assessed by the 6-Minute Walk Test (6MWT) in ambulatory patients.

Secondary objective 6 of this clinical investigation is to investigate the changes in functional mobility after a 4-week RAGT as assessed by the Timed Up and Go test (TUG) in ambulatory patients.

Secondary objective 7 of this clinical investigation is to investigate the changes in dynamic balance after a 4-week RAGT as assessed by the Four-Square Step Test (FSST) in ambulatory patients.

Secondary objective 8 of this clinical investigation is to investigate the changes in trunk movement after a 4-week RAGT as assessed by the Trunk Control Test (TCT) in non-ambulatory patients.

Secondary objective 9 of this clinical investigation is to investigate the changes in the limits of stability with respect to trunk movements after a 4-week RAGT as assessed by the Modified Functional Reach Test (MFRT) in non-ambulatory patients.

Secondary objective 10 of this clinical investigation is to investigate the changes in fall-related self-efficacy after a 4-week RAGT as assessed by the Falls Efficacy Scale- International Version (FES-I).

Secondary objective 11 of this clinical investigation is to investigate the changes in health-related quality of life (HRQoL) after a 4-week RAGT as assessed by the 5-level EQ-5D version (EQ-5D-5L).

Secondary objective 12 of this clinical investigation is to investigate the changes in depression after a 4-week RAGT as assessed by the Beck Depression Inventory, second edition (BDI-II).

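### The MFRT rule does not keep the baseline landmark or start position at the second test, so a pre-post difference can include an artefact that is not trunk change

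*Protocol*

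**What the plan says.** Secondary objective 9 (protocol section 2.3) concerns "changes in the limits of stability with respect to trunk movements after a 4-week RAGT", assessed by the MFRT in non-ambulatory patients. Table 7 schedules the test at baseline and post-intervention. The planned statistical analysis lists the MFRT as continuous, so the change goes into a paired t-test on the total sample.

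The standardised assessment description in section 4.8 sets out the measurement for severely affected, non-ambulatory stroke patients in the subacute stage:

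- **Default landmark:** "measure is taken from the distal end of the third metacarpal along the meterstick".
- **Fallback landmark:** "If the patient is unable to raise the affected arm, the distance covered by the acromion during leaning is recorded".
- **Start position, one sentence:** "Initial reach is measured with the patient sitting against the wall with an upper limb flexed to 90" degrees.
- **Start position, next sentence:** "The initial reach is measured with the patient sitting against the back of the chair with the upper limb flexed to 90 degrees".
- **Conditions:** one forward lean with the unaffected side at the wall, and a lean to each side with the back to the wall. Each has three trials, the first being practice. Distances are recorded per direction.

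The same section requires walking aids to be kept consistent and documented from test to test for the 10MWT and 6MWT. The MFRT has no such sentence for landmark or start position.

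**The concern.** The choice of landmark depends on whether the arm can be raised, and that can differ between visits. The description is for subacute stroke, and section 1.1 says that "recovery of walking and further sensorimotor and cognitive functions mainly takes place within the first 11 weeks after a stroke". Patients also receive their usual physiotherapy and occupational therapy throughout (section 7.4). It is therefore foreseeable that someone who cannot raise the arm at T1 can do so four weeks later. Followed literally, the text then takes acromion travel at T1 and hand travel at T2. Hand travel can include arm and shoulder movement that acromion travel leaves out, so the difference is not purely a trunk measure.

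The start-position sentences raise a similar problem. They describe the same initial reach in two ways, and a different choice at T2 than at T1 would enter the change score.

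The group is very small and uncontrolled. Section 8.1 (General aspects of the analysis) also allows a single improved case to be picked out and explored for causal explanation, so one artefact could matter beyond the mean.

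**Working it through.** **Inputs from the protocol.** Section 5.3 plans 5 patients with severe subacute stroke. The stated total reproduces: 4 groups × 5 + 4 groups × 2 = 28. Significance is two-tailed at 0.05. The protocol gives no effect size, SD or sample-size calculation for the MFRT.

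**Assumptions.** The documents give no difference between hand and acromion travel for the same lean. I call it *d* (T2 landmark minus T1 landmark, same trunk lean) and take an absolute size of 0 to 10 cm with either sign. The number of patients who switch, *k*, is also assumed. The number tested is *n* = 5; Table 7 refers to non-ambulatory patients generally, so *n* could be larger and the shift would shrink in proportion.

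**Step 1: which directions are exposed.** In the forward lean the unaffected side is at the wall, so the sound arm is presumably read. The lean to the unaffected side can use the sound arm as well. On a sensible reading, that leaves the lean towards the affected side, although the fallback sentence itself carries no such limit.

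**Step 2: mean shift with no true trunk change.** A patient with the same landmark at both visits contributes 0, and a patient who switches contributes *d*. The shift in mean change is *k* × *d* / *n*.

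| Absolute *d* | *k* = 1 | *k* = 2 |
|---|---|---|
| 0 cm | 0 | 0 |
| 2 cm | 2/5 = 0.4 cm | 4/5 = 0.8 cm |
| 5 cm | 5/5 = 1.0 cm | 10/5 = 2.0 cm |
| 10 cm | 10/5 = 2.0 cm | 20/5 = 4.0 cm |

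If the three directions were averaged and only one is exposed, the shift is *k* × *d* / 15. At 10 cm and one switcher that is 10/15 = 0.67 cm.

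**Step 3: sign.** Two illustrative cases, not document figures, show that the sign is open. Take an acromion 50 cm above the seat, an arm of 60 cm, and a sideways lean of 20 degrees.

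- Acromion travel: 50 × sin 20° = 17.1 cm.
- Hand travel with the arm fixed relative to the trunk: 17.1 − 60 × (1 − cos 20°) = 17.1 − 3.6 = 13.5 cm, so *d* is negative.
- With the arm kept level the two are about equal. If the shoulder reaches outwards, the hand travels further and *d* is positive.

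**Step 4: effect on the paired t-test.** Simulation used 100,000 runs, *n* = 5, no true change, an assumed SD of change of 3 or 5 cm, and offsets of 2, 5 and 10 cm. By symmetry the results hold for either sign.

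| Patients shifted | Rejection rate |
|---|---|
| 0 | 0.05 |
| 1 | 0.02 to 0.05 |
| 2 | 0.05 to 0.09 |
| 3 | 0.07 to 0.24 |
| 5 | 0.11 to 1.00 |

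One switcher does not raise the false-positive rate, because the outlying value also inflates the SD. High rates need most or all patients to shift the same way, for example if every patient were started differently at T2.

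**Step 5: start position.** Distance covered is final reach minus initial reach. If the start is the same at both visits, an offset common to both largely cancels in the change. Only a start that differs between T1 and T2 contributes, and the formula in Step 2 then applies with *d* as the start offset.

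**The case against.** The text gives a fallback for patients who cannot raise the arm and is silent on T1 against T2, so a switch is implied and not stated. That is right, and the point is limited to what can happen.

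Section 1.1 also says that milder paralysis recovers faster, and the exposed stratum is the severe one, followed for four weeks. The protocol gives no rate for regaining arm elevation, so one or two switchers among five is an assumption.

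The two start positions may belong to different conditions, since the side leans have the back to the wall and the forward lean does not. That is plausible, but the text does not say so. It does mean that simply deleting one sentence could remove a needed instruction.

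Assessors are trained for consistency (sections 6.4 and 7.1), and the CRF and the assessment manuals in the site file (section 10.2) are not shown. These may reduce variation between testers, but nothing shown settles either point. The triple measurement cited in section 10.6 repeats trials within a visit and does not address a landmark difference between visits.

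A reader might infer that the rule systematically creates apparent trunk improvement. The documents do not support that: no offset is given, and Step 3 shows that its sign depends on arm position. A reader might also infer a high risk of a falsely significant result. With one or two switchers the simulated rate is 0.02 to 0.09, so the concern is a distorted estimate of change.

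**Conclusion.** The point holds in a limited form. Section 4.8 lets the MFRT landmark follow arm ability when tested, does not carry the T1 landmark over to T2, and gives two unassigned start positions. For a patient who regains arm elevation, or who is started differently at T2, the change score can contain a measurement artefact, mainly in the lean towards the affected side.

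Under the assumed absolute offset of 0 to 10 cm, one such patient among five moves the mean change in that direction by up to 2 cm either way. The offset, its sign and the number of switchers are not in the documents. One secondary endpoint in a small group is affected; the feasibility criteria are untouched. This is a cheap improvement to the measurement rule and does not threaten the study's main conclusion.

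**What to change.** In section 4.8 and the matching CRF page:

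1. Fix the landmark per patient and direction at T1 and use the same one at T2, even if the arm can then be raised. Alternatively, record acromion travel on the affected side at both visits for every patient tested.
2. Reconcile the two start-position sentences by stating which applies to which test condition, and use the same start position at both visits.
3. Record landmark and start position in the CRF for each direction.
4. Compute change only from values with the same landmark and start position.

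The cost is a few sentences and CRF fields, with no additional test. The downside is that reach regained through the arm will not show in a direction where the acromion is kept, but that is not what secondary objective 9 measures.
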